### Follow-up of families

When the children turn four years-old, mothers receive an invitation to fill in a follow-up questionnaire regarding their own and their child’s eating and PA habits. This can be done in web-based or paper-based format. The questionnaire is delivered in conjunction with return of the accelerometer. In case of no response, families are reminded on three consecutive Mondays by postal mail. Families that cannot be reached by mail are called, or contacted via the short text message service (SMS).

Families who move to another CHC that is not participating in the trial are requested to provide follow-up data. The measurements are taken either at the new CHC or during home visits by trained research assistants.

### Replacement of intervention and control nurses

Whenever a nurse drops out of the study, the administrative head of the CHC should, according to the contract signed with the principal investigator, appoint a replacement nurse for the families concerned. Nurses replacing an intervention nurse follow the same five-day educational programme described above. However, nurses who are unable to attend this standard training programme are offered an alternative. They first meet with the central project coordinator for a general introduction and practical information on tasks and responsibilities, which is followed by a full day of MI training with the project’s senior psychologist. Thereafter, there is distance training, based on the intervention manual, educational movies and a presentation of the standard course, which is available on the project’s website (accessible only with a user-ID and password). The material concerns SCT, MI, and also nutrition and PA. Most importantly, four supervision sessions are offered, based on the nurses’ own MP3-recorded training sessions (as in the standard training programme described above).

### Statistical analysis

Based on variance estimates from similar Swedish data on 4-year-olds, we have estimated that the statistical power is approximately 90% to detect a mean BMI unit difference of 0.3 kg/m^2^ at four years of age. This assumes 410 children in the intervention group and 540 children in the control group (with group sizes based on mothers who filled in the baseline questionnaire in time, and excluding drop outs).

At four years of age, the BMI and WC of the participating children and their mothers will be compared between the intervention group and the control group, taking into account the cluster-randomised study design [35]. Primary analyses will include intention-to-treat analysis and per-protocol analysis.

For comparison of baseline characteristics (Tables 2, 3 and 4) we performed t-tests for continuous variables and χ^2^-tests for categorical variables, which were derived from un-adjusted linear and multinomial regression models with robust (sandwich) variance estimators [35], using Stata/IC 12.1 software (StataCorp, College Station, Texas, USA).

**Table 2 T2:** Baseline characteristics of the mothers

	**Intervention (n = 489)**	**Control (n = 550)**	
	**% (n)/Mean (SD)**	**% (n)/Mean (SD)**	**p-value**
**Age**	30. 3 (5.1)	29.4 (5.0)	0.108
**Education**			0.306
Primary	2.7 (13)	2.9 (16)	
Secondary	30.2 (149)	37.1 (204)	
Post-secondary	66.8 (327)	59.7 (328)	
**Born in Sweden**	94.7 (463)	91.1 (501)	0.036
**Smoking**			0.904
Current	8.0 (39)	8.9 (49)	
Former Smoker	26.4 (129)	27.5 (151)	
Never Smoker	65.6 (321)	63.6 (350)	
**BMI**	24.5 (4.5)	24.7 (4.8)	0.494
**BMI categories**			0.959
Underweight	2.5 (12)	2.7 (15)	
Normal weight	60.8 (295)	59.3 (325)	
Overweight	24.1 (117)	24.5 (134)	
Obese	12.6 (61)	13.5 (74)	
**Waist circumference (cm)**	83.7 (11.3)	84.2 (11.6)	0.494
**General Health Status**			0.941
Very good	22.1 (108)	23.7 (130)	
Good	58.2 (284)	58.2 (319)	
Fairly good	17.2 (84)	15.9 (87)	
Bad	2.3 (11)	2.0 (11)	
Very bad	0.2 (1)	0.2 (1)	

**Table 3 T3:** Baseline eating and physical activity habits of the mothers

	**Intervention (n = 489)**		**Control (n = 550)**		**p-value**
	**Mean (SD)**	**Median**	**Mean (SD)**	**Median**	
**Eating habits**					
Fruit (t/d)	1.4 (1.0)	1.0	1.2 (1.0)	1.0	0.071
Vegetables (t/d)	2.0 (1.2)	1.8	2.1 (1.5)	1.7	0.568
Fish (t/w)	1.7 (1.8)	1.4	1.6 (1.4)	1.4	0.509
French fries (t/m)	1.4 (1.8)	1.0	1.5 (1.9)	1.0	0.298
Sugared drinks* (t/w)	2.3 (3.3)	1.2	2.6 (3.6)	1.4	0.134
Discretionary calories** (t/w)	9.6 (5.9)	8.5	9.9 (6.3)	8.9	0.425
Having breakfast (t/w)	6.7 (1.1)	7.0	6.5 (1.3)	7.0	0.207
**Physical Activity**					
Work	2.8 (0.7)	2.9	2.9 (0.7)	3.0	0.207
Sport	2.6 (0.7)	2.5	2.5 (0.7)	2.5	0.341
Leisure	3.0 (0.7)	3.0	3.0 (0.6)	3.0	0.636

t = times, d = day, w = week, m = month. *Sugared drinks include soda with sugar, lemonade, and chocolate drinks; **Discretionary calories include savoury snacks, sugared drinks, sweets, chocolate, pastries, cake, and ice cream.

**Table 4 T4:** Baseline characteristics of the children

	**Intervention (n = 485)**	**Control (n = 556)**	
	**Mean (SD)**	**Mean (SD)**	**p-value**
**3 months of age**			
BMI (kg/m^2^)	16.0 (1.4)	16.2 (1.4)	0.019
Height (cm)	61.2 (2.6)	61.3 (2.4)	0.494
Weight (kg)	6.0 (0.8)	6.1 (0.8)	0.027
**6 months**			
BMI	17.2 (1.5)	17.3 (1.5)	0.053
Height	67.5 (2.4)	67.8 (2.4)	0.337
Weight	7.8 (0.9)	8.0 (0.9)	0.01
**9 months**			
BMI	17.3 (1.4)	17.5 (1.4)	0.068
Height	72.1 (2.5)	72.3 (2.5)	0.024
Weight	9.0 (1.0)	9.2 (1.0)	0.01
**Mean age at baseline**	6.7 (1.1)	6.7 (1.0)	
BMI	17.2 (1.5)	17.4 (1.5)	0.077
Height	68.5 (2.9)	68.7 (3.0)	0.433
Weight	8.1 (1.0)	8.2 (1.1)	0.041
**Current feeding mode**			0.956
Breastfeeding only	9.6 (47)	8.6 (47)	
Part-time	50.5 (247)	49.9 (274)	
Not any longer	36.6 (179)	38.3 (210)	
Never	3.3 (16)	3.3 (18)	

### Cost-effectiveness analysis

A cost-effectiveness analysis (CEA) will be conducted from a health care (payer) perspective, and a cost-utility analysis (CUA) from a long-term societal perspective. In the CEA, we will estimate the direct costs that would be incurred by an agency, e.g., a county council, in implementing this type of intervention, by comparing the intervention with care as usual with regard to differences in costs (incremental costs) divided by differences in health effects. The outcome will be the incremental cost-effectiveness ratio (ICER), which represents the additional cost of a one BMI-unit lower body weight among children in the intervention group compared with the control group. The time consumption of CHC nurses and parents in the intervention and control groups for all visits to their CHC from the ages of nine months to four years is recorded prospectively. Indirect costs mainly consist of parents’ absence from work due to their participation in the intervention. BMI at the age of four years is fairly strongly associated with BMI in adolescence and later life [36-38]. Based on our own empirical data [39] and data from the literature on risks of morbidity and mortality, we will estimate future productivity losses, e.g., due to disability pension and preterm mortality, and additional societal costs for one additional year of life gained by the intervention compared with care as usual.

## Results

### Baseline characteristics

The baseline questionnaire was administered at CHCs after obtaining informed consent from the families (n = 1369). Of the mothers who consented, 489 in the intervention group completed the questionnaire before the first intervention session. Due to time delays, an additional 46 mothers filled in the questionnaire after their first intervention session, and have therefore not been considered in the current results. In the control group, 550 mothers filled in the questionnaire before their children were 10 months of age (included here), but an additional 87 mothers filled in the questionnaire at a later stage (not included here).

The baseline characteristics of the 1039 mothers (with 1053 children) are presented in Tables 2, 3 and 4. Differences in the number of children and mothers are due to mothers with twins or triplets and or mothers who answered the questionnaire in time but quit before we had chance to collect growth data. At baseline, the mothers had a mean age of 30.3 (SD = 5.1) years in the intervention group, and 29.4 (SD = 5.0) years in the control group. Slightly more mothers were born in Sweden in the intervention group (94.7%) than in the control group (91.1%). The proportion of mothers with post-secondary education was somewhat higher among mothers in the intervention group (66.8%) than among those in the control group (59.4%). The proportion of mothers with overweight or obesity at baseline was similar in the intervention group (36.7%) to that in the control group (38.0%) (Table 2). The baseline eating and PA patterns of the mothers are presented in Table 3. Overall, there were no significant differences with exception of country of birth between the intervention and control groups, indicating successful randomisation. At nine months of age, the children had a BMI of 17.3 (SD = 1.4) kg/m^2^ in the intervention group, and 17.5 (SD = 1.4) kg/m^2^ in the control group (Table 4).

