### Participants

The eight counties (Stockholm, Uppsala, Södermanland, Örebro, Gävleborg, Västernorrland, Västmanland, and Jämtland) were selected on the basis of their relative closeness to Stockholm and/or accessibility. Approximately 37% of the Swedish population lives in these eight counties. When recruitment started in 2008, 1007 CHC nurses were employed in the eight counties and were invited to participate. Of these nurses, 129 (12.8%) agreed to participate in the trial. Before recruitment of a CHC nurse to the PRIMROSE trial, a contract regulating mutual responsibilities was signed between the administrative head of the CHC in question and the principal investigator (FR).

To assess any potential selection bias, all nurses working at CHCs in the participating counties were requested to respond to a questionnaire concerning their education and training, as well as the number of children for whom they were professionally responsible. Of the 1007 nurses, 701 (69.9%) responded to the questionnaire. At baseline, trial nurses had a mean age of 48.3 (SD = 9.0) years and had worked as a CHC nurse for an average of 10.6 (SD = 8.3) years. A majority of trial nurses (68%) had specialist training in primary health care, while 30% had a specialist education in child and adolescent health (compared with 74% and 26%, respectively, of all CHC nurses in the study area). Among the trial nurses, 63% had already received some type of short MI training prior to enrolment as a trial nurse (compared with 56% among all nurses). The number of preschool children for whom a nurse was responsible did not differ between trial nurses (mean = 45.2, SD = 21.8) and non-trial nurses from the same region (mean = 49.0, SD = 22.3).

First-time parents receiving preventive services at a participating CHC (n = 2230) were asked by the trial nurses whether they wished to participate when their children were 5-6 months of age. Families were excluded if they did not speak Swedish (n = 172), were about to change their CHC (n = 49), or had severe social family problems making it unethical to ask them to participate (n = 67), or for other (non-reported) reasons (n = 75). A total of 1867 families were eligible for participation, of which 1369 (73.3%) agreed to participate in the trial (see Figure 1).

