### Measurements

At four years of age, the Body Mass Index (BMI) and waist circumference (WC) of the participating children and their mothers will be compared between the intervention group and the control group. Four-year-old children’s BMI and WC are the primary outcomes, and will be used as indicators of obesity status. CHC nurses weigh and measure the children on validated scales and stadiometers. Since BMI is rarely measured at exactly four years of age at CHCs, we will predict BMI at four years using a non-parametric regression method called kernel smoothing [27]. International definitions are used to classify children’s body sizes as underweight, normal weight, overweight, or obese [28].

Secondary outcomes are mothers’ BMI and WC, children’s and mothers’ PA and eating habits, and also parental self-efficacy (PSE). The eating habits of children and mothers are assessed with a FFQ that includes questions about habitual dietary intake of certain food items as well as intake of beverages, and is complemented by questions about regularity of breakfast eating. Parents record their children’s food intake at home but not the children’s intake during day-care. Mothers, on the other hand, record their complete dietary intake. The dietary outcome variables evaluated in the PRIMROSE study concern fruit, vegetables, fish, French fries, sugared drinks, discretionary calories, and the regularity of breakfast eating. The concept of discretionary calories was introduced by the Swedish National Food Agency, and is a collective name for products that have little nutritional value, but are high in energy, e.g., savoury snacks, sugared drinks, sweets, chocolate, pastries, cakes and ice cream.

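### The article reports no baseline difference beyond country of birth, yet its Table 4 shows intervention children lighter before treatment, and no baseline adjustment of 4-year BMI is named

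*Protocol article*

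**What the plan says.** The Baseline characteristics section introduces the mothers' and children's data in Tables 2, 3 and 4 together and concludes: "Overall, there were no significant differences with exception of country of birth between the intervention and control groups, indicating successful randomisation". The next sentence gives child BMI at nine months, 17.3 against 17.5.

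On outcomes, the Measurements section states: "Four-year-old children’s BMI and WC are the primary outcomes". The Statistical analysis section says that 4-year BMI and WC "will be compared between the intervention group and the control group, taking into account the cluster-randomised study design". It names no covariate. The word un-adjusted does occur in that section, but it describes the tests behind the baseline tables, not the outcome model.

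Measurements also says "we will predict BMI at four years using a non-parametric regression method called kernel smoothing". That step deals with the age at which the outcome is measured. It does not adjust for baseline size.

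The planned size is given as: "the statistical power is approximately 90% to detect a mean BMI unit difference of 0.3 kg/m^2^ at four years of age". The group sizes behind that figure are 410 (intervention) and 540 (control).

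**The concern.** The balance statement does not agree with the p-values in Table 4, which already use a robust variance estimator. The variable out of balance is the infant version of a primary outcome, and the difference favours the intervention arm before any session has been held.

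Whole units were randomised, and families in those units "were asked by the trial nurses whether they wished to participate when their children were 5-6 months of age". With 59 units, chance alone can leave families unequal, so balance has to be looked at and handled rather than assumed.

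A comparison of 4-year means without infant BMI would credit part of the existing gap to the intervention. The same BMI difference is the denominator of the planned cost-effectiveness ratio, so the error would pass into that as well. The Discussion says background factors need to be accounted for in the dietary outcomes. Nothing similar is said for BMI, and a statement that the groups are balanced takes away the visible reason to adjust.

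**Working it through.** **1. The plan's own figure.** The article gives about 90% power for 0.3 kg/m2 with 410 and 540 children. SD, alpha and intracluster correlation (ICC) are not stated. Assuming two-sided 5% and no clustering, the SD that gives 90% is

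0.3 / [(1.960 + 1.282) × √(1/410 + 1/540)] = 0.3 / (3.242 × 0.0655) = 1.41.

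Power is 94% at SD 1.30, 90% at 1.41 and 86% at 1.50. The stated figure is attainable but cannot be confirmed. SD 1.41 is used below as an assumption.

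**2. Child size in Table 4 (485 intervention, 556 control).**

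| Age | BMI, int. vs control | Difference | p | Weight (kg) | p |
|---|---|---|---|---|---|
| 3 months | 16.0 vs 16.2 | -0.2 | 0.019 | 6.0 vs 6.1 | 0.027 |
| 6 months | 17.2 vs 17.3 | -0.1 | 0.053 | 7.8 vs 8.0 | 0.01 |
| Baseline (mean 6.7 months) | 17.2 vs 17.4 | -0.2 | 0.077 | 8.1 vs 8.2 | 0.041 |
| 9 months | 17.3 vs 17.5 | -0.2 | 0.068 | 9.0 vs 9.2 | 0.01 |

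Weight has p<0.05 at all four points and BMI at one. Height at 9 months is also listed with p=0.024, but 72.1 vs 72.3 (SD 2.5) gives about 0.20 in an unclustered test, and 0.053 at the extreme of rounding. That row is not relied on here.

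**3. Timing.** The intervention section puts the first session at about nine to ten months; the abstract puts the programme's start at 8-9 months. The two need to be reconciled. On either reading the 3-month, 6-month and 6.7-month values come before the intervention. The 9-month values are not securely so.

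**4. Carry-over to age 4 with no intervention effect.** Carry-over = r × (SD at 4 years / SD in infancy) × gap. The correlation r between infant and 4-year BMI is not in the article; 0.3-0.6 is assumed. With SDs 1.41 and 1.4 and a gap of 0.2:

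- r = 0.3: 0.3 × 1.007 × 0.2 = 0.06
- r = 0.4: 0.08
- r = 0.5: 0.10
- r = 0.6: 0.12

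This is 20-40% of the 0.3 target. Each mean is rounded to 0.1, so a printed gap of 0.2 may be anything from about 0.1 to 0.3. The range then widens to 0.03 (gap 0.1, r 0.3) through 0.18 (gap 0.3, r 0.6).

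**5. False-positive rate of the unadjusted test, given the gap.** SE = 1.41 × √(1/410 + 1/540) = 0.0924. Given the gap, the residual SE is 0.0924 × √(1 - r²), and rejection still occurs beyond ±1.96 × 0.0924 = ±0.181.

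- r = 0.3: residual SE 0.0881. Upper-tail z = (0.181 - 0.060)/0.0881 = 1.37; with the small other tail, about 9%.
- r = 0.6: residual SE 0.0739. Upper-tail z = (0.181 - 0.121)/0.0739 = 0.81; about 21%.

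With an assumed ICC of 0.01-0.03 and 57 degrees of freedom, the same calculation gives about 7-16%. With a true gap of only 0.1 and no clustering it returns to about 5%.

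**6. Gain from adjustment.** Replacing SD 1.41 by 1.41 × √(1 - r²) raises nominal power from 90% to about 93-98% for r = 0.3-0.6, clustering ignored.

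**The case against.** **The sentence may concern mothers only.** It follows the remarks on Tables 2 and 3, and for those tables it is true: country of birth (p=0.036) is the only p below 0.05. But the paragraph opens with all three tables, the sentence carries no restriction to mothers, and child BMI comes next. At best it is ambiguous.

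**The significant rows are not independent.** BMI and weight in the same children over a few months amount to something close to one imbalance seen repeatedly. This stands, so counting rows adds little. For BMI itself three of the four p-values are 0.053-0.077. What matters for bias is the size of the gap and how strongly it predicts the outcome, not how many p-values fall below 0.05.

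**A reader might infer that the outcome analysis is planned without baseline BMI.** The article does not say so. It is silent, and a covariate set is commonly left to an analysis plan, which is not shown here. The point is therefore conditional: no adjustment is named despite a visible imbalance.

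**A reader might infer that randomisation failed, or that nurses recruited selectively.** Neither is shown. Chance imbalance is ordinary with 59 units, and the text does not set out acceptance by arm or whether allocation was known when families were invited.

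**The size is uncertain.** The correlation, the SD and the ICC are assumptions. Table 4 covers 485 and 556 children against 410 and 540 in the power statement, so the gap in the analysed set may differ.

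**Conclusion.** The balance statement is wrong as written for the children, on the article's own p-values: 3-month BMI and weight at all four time points. BMI in the intervention arm was 0.1-0.2 kg/m2 lower before the first session, against a target of 0.3.

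The analysis part holds conditionally. If 4-year BMI is compared with allowance for clustering alone, about 0.06-0.12 kg/m2 of apparent benefit would be expected with no true effect. That rests on an assumed correlation of 0.3-0.6 and a gap of 0.2; rounding widens it to about 0.03-0.18. The full 0.2 would not be expected to persist at these correlations. If the unseen analysis plan already adjusts for infant BMI, only the reporting error remains.

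**What to change.** 1. In Baseline characteristics, limit the statement of no differences to the mothers' tables. Report that intervention children had lower weight at every time point and lower BMI (p=0.019 at 3 months; 0.053-0.077 otherwise). Delete the inference that randomisation succeeded.

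2. In Statistical analysis, state that the primary child BMI model, allowing for clustering, includes pre-intervention child BMI as a covariate. Choose one value in advance: the 3-month value or the one at about 6.7 months. The 9-month value is too close to the first session. Give the unadjusted result as secondary. If the analysis plan already does this, cite it.

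The reason given for the covariate should be that it is the infant measure of the outcome, not that a baseline test was significant.

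Sex, country of birth and education may be added but are optional. Child WC has no infant value in Table 4, so this change concerns BMI.

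The cost is two or three sentences and no new data. Follow-up was still running when the article was submitted, so the covariate could be fixed before the outcome comparison.

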### Relative validity of the FFQ

Of the 2400 invited families, 514 (21.5%) agreed to participate. Sixty-eight percent of the mothers who wanted to participate completed the first 4-day FD. The second 4-day FD, which was sent to those who completed the first, had a response rate of 78%. The FFQ was sent to those families who had completed at least one of the two FDs. The relative validation was carried out among 214 mother-child pairs that had completed both 4-day FDs and the FFQ (response rate: 8.9%). Half of the children in the sample were girls, and mean age in the sample was 4.0 (SD = 1.0) years. According to self-reports of height and weight, 12% of the children were either overweight or obese. The mothers had a mean age of 37.2 years (SD = 4.4), and a mean BMI (self-reported) of 23.3 kg/m^2^ (SD = 3.9), and were relatively highly educated (61% with 3 years or more of post-secondary education). A majority of the mothers (92%) were born in Sweden, and 19% were overweight or obese. The time period between the recording of the first and the second 4-day FD was on average 24 days (range 8-85), and between the second 4-day FD and the FFQ, 23 days (range 3-141).

The mean and median frequencies of intakes of food and beverages reported in the FFQ and the 8-day FD, for children and mothers, are presented in Table 5. The differences between mean frequency intake values according to the FFQ and FD show that the FFQ provided higher estimates than the FD for a majority of the food groups, with the exception of sugared drinks.

**Table 5 T5:** Relative validity of the food frequency questionnaire (FFQ)

	**Food diary**			**FFQ**			**Food diary and FFQ**				
	**Mean**	**SD**	**Median**	**Mean**	**SD**	**Median**	**n**	**d†**	**95% CI**	**r**	**95% CI**
Children											
Fruits (t/d)	0.89	0.55	0.79	1.19	1.07	1.00	210	0.30	0.19; 0.42	0.42	0.31; 0.53
Vegetables (t/d)	0.74	0.38	0.71	1.83	1.11	1.57	212	1.08	0.96; 1.19	0.48	0.36; 0.58
Fish total (t/w)	1.11	1.06	1.00	1.65	1.68	1.47	211	0.54	0.33; 0.74	0.31	0.18; 0.42
French fries (t/m)	1.21	2.00	0.00	1.36	1.50	1.00	210	0.14	-0.12; 0.40	0.36	0.24; 0.48
Sugared drinks* (t/w)	2.80	2.65	2.00	2.41	2.90	1.50	211	-0.39	-0.65; -0.13	0.59	0.50; 0.67
Discretionary calories** (t/w)	8.38	4.39	8.00	9.16	5.79	8.05	212	0.75	0.18; 1.33	0.56	0.46; 0.65
Mothers											
Fruits (t/d)	1.15	0.75	1.07	1.63	1.09	1.43	213	0.48	0.37; 0.59	0.60	0.50; 0.68
Vegetables (t/d)	1.31	0.49	1.29	2.76	1.40	2.57	213	1.44	1.29; 1.59	0.32	0.19; 0.43
Fish total (t/w)	1.86	1.53	1.50	2.25	1.92	2.00	205	0.36	0.13; 0.60	0.41	0.28; 0.51
French fries (t/m)	0.99	1.91	0.00	1.23	1.54	1.00	211	0.23	0.00; 0.46	0.34	0.22; 0.46
Sugared drinks* (t/w)	1.43	1.89	1.00	1.33	1.94	0.75	209	-0.13	-0.37; 0.11	0.43	0.32; 0.54
Discretionary calories** (t/w)	8.29	4.29	8.00	8.51	5.60	7.42	198	0.19	-0.45; 0.83	0.52	0.41; 0.61

r = Spearman correlation, t = times, d = day, w = week, m = month, CI = confidence interval. *Sugared drinks include soda with sugar, lemonade, and chocolate drinks; **Discretionary calories include savoury snacks, sugared drinks, sweets, chocolate, pastries, cake, and ice cream. †Difference between mean FFQ and mean food diary.

The results show that there were strong correlations between the FD and the FFQ for mothers’ fruit intake. Moderately strong correlations were found for children’s fruit and vegetable intake, mothers’ and children’s intake of discretionary calories, mothers’ intake of fish, and mothers’ and children’s intake of sugared drinks. Weak correlations were seen for children’s fish intake, mothers’ and children’s intake of French fries, and mothers’ vegetable intake (Table 5). Graphical evaluation of Bland-Altman plots showed that most of the observations fell within the 95% limits of agreement (data not shown). In general, there was an increase in the differences between the results of the two methods as intake increased. While agreement between the two methods was fairly good at lower levels of intake of vegetables among both children and mothers, the differences increased with increasing vegetable intake, suggesting over-reporting in the FFQ compared with the FD at higher levels of intake. For both children’s and mother’s fruit intake, there was a systematic negative difference at lower intakes and a positive difference at higher intakes.

Mothers with normal weight, compared with overweight, tended to be more accurate in reporting of their own fruit intake (r = 0.67 vs. r = 0.35), their child’s fruit intake (r = 0.50 vs. r = 0.08), and their own intake of discretionary calories (r = 0.57 vs. r = 0.37). Mother’s with normal weight were also more accurate in reporting of their child’s fish intake (r = 0.29 vs r = 0.06). However, there were stronger relationships between the FD and the FFQ for maternal vegetable intake among mothers with low education compared with mothers with high education (r = 0.48 vs. 0.18).

